#### Assessment of trial feasibility

The primary feasibility outcomes of this study include: (i) number of participants at each stage of the study, at each site, with stages including: identified as potentially eligible, approached, consented to study, completed screening and baseline, randomised (with at least five participants being recruited at each site), completed treatment and completed outcome assessments; (ii) any difficulties experienced at sites that may affect their ability to recruit in future will be identified and reviewed; (iii) evaluation of appropriateness of the trial and economic evaluation methods and procedures; (iv) assessment of participants’ willingness to be randomised to treatment allocation; (v) adherence to treatment assessed as number of sessions completed, a session will be recorded as complete if the participant has been through every page, reached the end and completed the coach web-linked session related to that material (with a target of participants completing at least five sessions) and (vi) attrition (with a target of at least 80% of participants completing follow-up assessments).

We will report the proportion of screened families who are found to be eligible, the proportion of eligible families who are recruited and randomised to their allocation and the proportion of randomised participants who provide outcome data at follow-up, with 95% CIs. Our sample size of 25 participants will allow us to estimate loss to follow-up (anticipated to be 20%) with a 95% CI of +/-13 percentage points. The further outcome is evaluation of the SD of the BRIEF-2 (parent) score for this patient population. This is the proposed primary outcome for the main trial and required for calculation of the sample size.^36^

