A two-arm randomised controlled feasibility phase II study will be conducted.^32^ The aim is to assess whether a larger, fully powered, definitive RCT and cost-effectiveness analysis can be successfully planned and delivered. In order to gain as much information as possible to inform a fully powered RCT, additional objectives are considered in this feasibility trial, including accessing information related to treatment set-up, delivery costs and resource use (table 1).

**Table 1 T1:** Study objectives

Number	Study objectives
1	Are clinicians able and willing to identify participants (eg, has time and access to database, medical records or clinic lists to identify potentially eligible patients)?
2	Are the online screening, consent and randomisation process feasible?
3	How many participants at each site are initially eligible, approached and consented, have completed screening and baseline questionnaires, been randomised (with a recruitment target of at least five participants per site), completed treatment and completed outcome assessments?
4	Do adolescents and parents find the intervention and outcome measures acceptable?
5	What are parents’ and adolescents’ experiences of study participation?
6	Is it possible to calculate means and SD for a full RCT for the potential primary outcome measure?
7	What resources will be required to run a main trial?
8	Do some sites need additional support to be able to recruit to target in a future trial?
9	Do the trial and economic evaluation methods and procedures yield the information required?
10	How willing are participants to be randomised and complete outcome measures?
11	How well do participants adhere to the intervention (number of sessions completed)?
12	How many complete and analysable data sets are yielded, and what is the level of missing data?
13	How many participants are lost to follow-up?
14	What is the coach’s experience of supporting intervention delivery?
15	What are adolescent and parent experiences of TAU? (TAU arm)

RCT, randomised controlled trial; TAU, treatment as usual.

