## Methods and analysis

This is a randomised, controlled, multicentre feasibility study in young patients with pABI aged 12 to 18 years. Twenty-five participants will be randomised (minimised by site and type of brain injury) in a 1:1 ratio to receive TAU or treatment as usual plus Teen Online Problem-Solving (TAU + TOPS UK). Treatment allocation will not be blinded. The protocol (V.4.1, 30 August 2018) is registered on Current Controlled Trials ISRCTN10906069 and follows Standard Protocol Items: Recommendations for Interventional Trial guidelines.^33^

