### Setting

Two settings will be utilised to examine feasibility outcomes associated with recruitment of adolescents known to have had a pABI:Direct referral by clinicians of adolescents who are under the outpatient care (usually neurology, neuropsychology or paediatric) of five participating NHS Trusts in England. Screening logs will be maintained at all sites to record the number of patients screened and enrolled in the study. These sites were selected to be representative of the range of types of services which might be included in a future trial, with TAU ranging from no provision through to services providing multidisciplinary outpatient care over the long-term.Recruitment from Participant Identification Centres (PICs) in primary or secondary care, or charitable organisations. Potential participants will respond directly to study promotion including leaflets/posters/participant information sheets distributed by parent-led groups, charities or support groups.

Study participation will be supported by research nurses at each participating NHS Trust. For participants directly referred to the study, nurses will make the first approach to the family. For those identified through PICs, families will be asked to contact the research nurse whose details are provided on the patient information sheet (PIS). The research nurse will support all families during the online consent and will be a point of contact for all participants during the study. The research nurse or other research team member will support baseline and follow-up measure completion. The intervention will be provided through online materials and video conference links with a coach trained in the TOPS-UK intervention. The coach will also receive weekly supervision from a qualified clinical psychologist on the research team to ensure treatment fidelity. The single study coach will be centrally based at the lead site.

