### Sample size calculation

The study will aim to screen 20 potential participants at each site (n=100 in total), and aim to recruit a sample size of 25 participants from five sites. This should provide sufficient data to assess the feasibility and acceptability of the study. Although the sample size for the full RCT will be estimated based on the minimum clinically important difference for the BRIEF score^35^ (5-points), the SD for this patient population is currently unknown. A sample size of 25 is considered a realistic target and would be sufficient to address the feasibility aims (ie, acceptability of questionnaires etc), as well as aiming to provide at least 12 participants reporting quantitative baseline data to calculate the required SD.^36^

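### The target of at least five participants at each of five sites leaves no slack against a total of 25, and would probably be missed even if recruitment went as planned

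*Protocol article*

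**What the plan says.** The per-site figure appears twice in the protocol article. Objective 3 in Table 1 asks for numbers at each stage by site, "with a recruitment target of at least five participants per site". The section on assessment of trial feasibility repeats it within the first primary feasibility outcome: "randomised (with at least five participants being recruited at each site".

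The total appears in several places. The sample size section words it as an aim: "aim to recruit a sample size of 25 participants from five sites". The opening of Methods and analysis words it as a number: "Twenty-five participants will be randomised (minimised by site and type of brain injury) in a 1:1 ratio". The abstract likewise gives 25 as the number to be recruited. The Setting section confirms the number of sites: "five participating NHS Trusts in England".

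Screening is also planned by site: "The study will aim to screen 20 potential participants at each site (n=100 in total").

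Objective 8 asks: "Do some sites need additional support to be able to recruit to target in a future trial"?

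The article does not say that recruitment closes at the 25th participant, that sites compete for places, or that any site is limited to five.

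**The concern.** Five sites with a minimum of five each use up all 25 places. A per-site minimum is normally set below the average, so that ordinary variation between sites does not breach it. Here the minimum equals the average. If the total is 25, any site that recruits six forces another to four or fewer.

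The purpose of the study is to judge whether a definitive trial is feasible, and the per-site figure is the only numerical recruitment threshold attached to a primary feasibility outcome. The sites were chosen to span different kinds of service, so uneven recruitment is to be expected. A threshold that even identical sites would seldom all meet cannot separate chance from a real recruitment difficulty. A reader of the results could take a missed site target as evidence against feasibility when the overall number was reached.

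**Working it through.** **Inputs**
- Sites: 5 (Setting; Sample size calculation).
- Minimum per site: 5 (Table 1, objective 3; Assessment of trial feasibility).
- Total: 25 (abstract; Methods and analysis; Sample size calculation).
- Screening: 20 per site, 100 in total (Sample size calculation).
- Assumed, because the article does not give them: the recruitment model, equal site rates, and independence between sites.

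**Step 1: the plan's own figure.** 5 sites × 5 participants = 25. The total is reproduced, and it equals the sum of the site minima with nothing over.

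**Step 2: allocations that meet both targets.** The number of ways to divide 25 participants among five sites is C(29, 4) = 23,751. The number with every site at five or more is C(25 − 25 + 4, 4) = C(4, 4) = 1, the even split.

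**Step 3: competitive recruitment stopped at 25 (assumption).** With equal site rates the counts are multinomial:

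P(5,5,5,5,5) = 25! / [(5!)^5 × 5^25] = 0.0021, or 0.2%.

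On average about 2.9 of the five sites reach five. If one site recruits at twice the rate of each of the others, the probability of meeting the target falls to about 0.08% (simulation, 400,000 draws).

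**Step 4: site-by-site recruitment without an overall cap (assumption).** The plan's numbers imply a conversion of 25/100 = 25%. For one site screening 20:

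P(X ≥ 5) = 1 − Σ(k = 0 to 4) C(20, k) × 0.25^k × 0.75^(20 − k) = 0.585.

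For all five independent sites: 0.585^5 = 0.069, or about 7%. The expected total is 5 × 20 × 0.25 = 25, so this is recruitment going as planned on average.

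**Step 5: how far above 25 the total would have to go.** Under equal-rate competitive recruitment stopped at N, the simulated probability that all five sites have at least five is:

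| N | P(all five sites ≥ 5) |
|---|---|
| 25 | 0.2% |
| 30 | 12% |
| 35 | 39% |
| 40 | 64% |
| 45 | 81% |
| 50 | 91% |

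The target becomes more likely than not to be met only at a total between 35 and 40.

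**Step 6: what one site's count can show.** The exact Poisson 95% CI for five events runs from about 1.6 to 11.7, a ratio of 11.7/1.6 ≈ 7. A site with four recruits is therefore not distinguishable from one with five or six.

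**The case against.** The strongest reply is that the targets agree: 5 × 5 = 25, and the sample size section reads naturally as a quota of 20 screened and five recruited at each site. On that reading the total is just the sum of the quotas. If each site carries on until it has five, or if 25 may be exceeded, a site that recruits six does no harm. Sites also have a second source of participants ("Recruitment from Participant Identification Centres (PICs) in primary or secondary care, or charitable organisations"), so 20 screened need not be a ceiling. The rule for closing recruitment may stand in the full protocol, which the article condenses.

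This stands in part. A reader might infer that the targets are incompatible, or that one successful site makes the target fail. The document supports neither as a general statement. The second needs a hard stop at 25: the wording in Methods and analysis leans that way, but the sample size section states an aim and no stopping rule is given. A reader might also infer that missing the site target means the study is declared a failure. The article states no such consequence; difficulties at sites are to be identified and reviewed.

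Nor does objective 8 rest on this count alone. It concerns recruitment to target in a future trial, and screening logs and interviews with research nurses also inform it.

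What the reply does not remove is the absence of slack. Under the quota reading, with the plan's own screening number and implied conversion, the chance that all five sites reach five is still only about 7%.

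**Conclusion.** The point holds as a badly set threshold, not as a contradiction. At 25 randomised, the site target is met by one allocation out of 23,751. The chance of meeting it is 0.2% under equal-rate competitive recruitment stopped at 25. It is about 7% if each site screens its own 20 at 25% conversion, independently and with no overall cap. Both recruitment models are assumptions; the article states neither. The target becomes attainable if recruitment may run well past 25, but the article calls 25 the realistic number.

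The consequence is limited: the target would probably be recorded as missed although recruitment went to plan, and a shortfall due to chance could be mistaken for a site problem. The screening logs and interviews soften this but do not repair the threshold. It is worth correcting because the figure belongs to a primary feasibility outcome.

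**What to change.** - In objective 3 and the first feasibility outcome, state the recruitment target as 25 overall, a mean of five per site, and drop the minimum at every site.
- Say whether 25 is a cap or may be exceeded, and whether sites recruit competitively or to a quota.
- Report for each site the number randomised and the rate per month open, with an exact Poisson 95% CI, as description only. Acknowledge that the intervals will be wide (about 1.6 to 11.7 for a count of five, divided by months open for the rate), so they show the uncertainty and do not rank the sites.
- State that a count below five is not by itself evidence of a site problem, and that it will be read together with the screening logs and nurse interviews already planned.

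The cost is a change of wording. Site opening and randomisation dates are routine trial data, and no extra participants are needed. The downside is a less sharp criterion at site level.

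### The 95% CI half-width for loss to follow-up is misstated: 25 participants with 20% loss give about +/-16 percentage points, not +/-13

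*Protocol article*

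**What the plan says.** Under Assessment of trial feasibility, attrition is the last of six primary feasibility outcomes, "with a target of at least 80% of participants completing follow-up assessments". The next paragraph says the trial will report "the proportion of randomised participants who provide outcome data at follow-up, with 95% CIs", and then gives the precision expected: with 25 participants the team expects to "estimate loss to follow-up (anticipated to be 20%) with a 95% CI of +/-13 percentage points". Sample size, anticipated proportion, confidence level and half-width thus all stand in one sentence.

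The Sample size calculation section gives the same number, as an "aim to recruit a sample size of 25 participants from five sites". It does not mention the 13 points. It says that "A sample size of 25 is considered a realistic target and would be sufficient to address the feasibility aims", and adds that at least 12 participants should give baseline data for the SD of the BRIEF score. No other confidence interval width appears in the article, and no interval method is named for this one.

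**The concern.** The sentence contains everything needed to check it, and its result does not follow from its inputs. The usual normal-approximation half-width for 20% in 25 is close to 16 points. The error is in the favourable direction: the trial looks better able to pin down attrition than it is.

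At stake is how a reader or funder judges what the trial can say about retention. Taken at face value, 20% +/- 13 points suggests that, if loss is as anticipated, true loss would be placed between 7% and 33%. The upper end matters most when a later trial is inflated for dropout, and that is where the stated interval falls short. If loss does come out at 20%, the reported 95% interval will also be visibly wider than the protocol promised.

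**Working it through.** **Inputs** (all from the sentence under Assessment of trial feasibility; the sample size is confirmed under Sample size calculation)
- n = 25 randomised participants
- p = 0.20 anticipated loss, consistent with the 80% completion target
- confidence level 95%, two-sided, z = 1.96
- stated half-width 13 points

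**Attempt to reproduce the stated figure**
- Standard error = sqrt(p(1 - p)/n) = sqrt(0.2 x 0.8/25) = sqrt(0.0064) = 0.080
- 95% half-width = 1.96 x 0.080 = 0.157, or 15.7 points (4.3% to 35.7%)

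The stated 13 is not reproduced. The shortfall is 15.7 - 13 = 2.7 points; the correct half-width is about a fifth larger (15.7/13 = 1.21).

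**Does another 95% method give 13?** With 5 of 25 lost:

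| Method | 95% interval | Half-width (points) |
|---|---|---|
| Normal approximation | 4.3% to 35.7% | 15.7 |
| t quantile, 24 df | symmetric | 16.5 |
| Normal with continuity correction | symmetric | 17.7 |
| Wilson | 8.9% to 39.1% | 15.1 |
| Jeffreys | 8.1% to 38.4% | 15.2 |
| Agresti-Coull | 8.4% to 39.6% | 15.6 |
| Clopper-Pearson (exact) | 6.8% to 40.7% | 16.9 |

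For the asymmetric intervals the half-width is half the total width. The range is 15.1 to 17.7 points, so none gives 13. The lower arm of the exact interval is 13.2 points, but its upper arm is 20.7, so a symmetric 13 does not describe it.

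**Which inputs would give 13?**
- Sample size at 95% and p = 0.20: n = 0.16 x (1.96/0.13)^2 = 36.4, so 37. Allowing for rounding to a whole point, n = 34 gives 13.45, so at least 34 would be needed.
- Proportion at 95% and n = 25: p of about 12.5% gives 13.0 points.
- Confidence level at n = 25 and p = 0.20: a 90% interval gives 1.645 x 0.080 = 0.132, or 13.2 points, which rounds to 13.
- Other denominators at 95% and p = 0.20: counting adolescents and parents separately (n = 50) gives 11.1 points; the 100 to be screened give 7.8. Neither is 13, and the article defines the proportion over randomised participants.
- A finite-population correction for 25 out of 100 gives 15.7 x sqrt(75/99) = 13.6, which rounds to 14 and has no basis in the text.

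**Effect on the implied range**
- Stated: 20 - 13 = 7% to 20 + 13 = 33%.
- Exact for 5 of 25: 6.8% to 40.7%. The upper limit is 40.7 - 33 = 7.7 points higher.

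**The case against.** The strongest case on the other side accepts the arithmetic and disputes its weight.

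First, the sample size was not derived from this figure. The article presents precision as something that 25 participants will allow. The number itself is defended under Sample size calculation as realistic, as enough for the feasibility aims, and as giving at least 12 participants for the SD; five sites with a target of at least five each also make 25. This stands. A reader might infer that the only numerical basis for 25 has collapsed, or that 25 is too few. The document supports neither inference.

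Second, nothing downstream uses the half-width. The Data analysis plan rules out a formal comparison, the 80% completion figure is a target with no stated rule that uses an interval, and the reported intervals will come from the data. The Follow-up questionnaires section also says that the definitive trial will allow for more attrition than is seen here. This stands too, and it limits the consequence.

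Third, a reader might go on to fault the plan for not naming exact or Wilson intervals, or for not saying what an observed 80% could establish. The choice of interval method is commonly left to a statistical analysis plan, which is not shown here, and the article makes no claim about what reaching 80% would prove. Neither is an error in this document.

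None of this rescues the figure. The sentence is complete and its own inputs contradict its result.

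**Conclusion.** The stated precision is wrong as written. With 25 participants, 20% loss and a 95% level, the half-width is 15.7 points by the normal approximation and between 15.1 and 17.7 points across the usual methods. The figure of 13 overstates precision by 2.7 points on the simplest reading. This rests only on the three inputs that the article itself states, with all 25 randomised participants as the denominator.

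A 90% multiplier labelled as 95% would explain the 13, but that is an inference; the document gives no other confidence level or sample size for this estimate. Since the same paragraph commits to 95% intervals for the feasibility proportions, the label cannot simply be read as 90%.

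The point is a correction to one number. It is worth making because it is the only interval width in the article and it describes a primary feasibility outcome. It does not put the sample size, the analysis or any decision rule in doubt.

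**What to change.** Under Assessment of trial feasibility, replace 13 percentage points by about 16 percentage points. Optionally add that the exact 95% interval is 7% to 41% if 5 of 25 are lost, which shows the asymmetry that a plus-or-minus figure hides. If 13 points at a 90% level was what was meant, relabelling the level would also make the sentence true, but it would then differ from the 95% intervals promised in the same paragraph, so restating the half-width is cleaner.

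The cost is one sentence. No extra participants and no change to the analysis are needed; the stated precision becomes somewhat less favourable.

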### Measurement of outcomes

This feasibility study aims to evaluate all aspects of the proposed fully powered RCT and cost-effectiveness analysis including recruitment and retention numbers, and completion of outcome measures proposed for the main trial. Outcomes will be assessed by questionnaires and interviews. Table 3 provides a summary of outcome measures for this feasibility trial.

**Table 3 T3:** Summary of outcome measures

Outcome group	Outcome measure	Objective	Evaluation time point(s)
Primary outcome (main trial)	Parent BRIEF-2	6	Baseline, 17 weeks post-randomisation
Secondary outcomes (main trial)	Adolescent: RCADS, SDQ, CBQ, BRIEF-2, CHU-9D Adult: RCADS, SDQ, EQ-5D-5L*, PHQ-9*, GAD-7*, CBQ, CSRI	1,10,11	Baseline, 17 weeks post-randomisation
Measures of adherence (intervention group)	Participation in weekly Skype sessions. Record of login to intervention website (frequency, duration, progression)	3,11	Data recorded by coach. Data captured automatically by database throughout 16 week intervention period.
Intervention feasibility and acceptability (intervention group)	Qualitative interviews with families Intervention acceptability questionnaires (adolescent and parent) Qualitative interview with coach	1–4, 6, 9	End of trial 17 weeks post-randomisation End of trial
Experience of TAU (TAU arm)	Qualitative interviews with families	15	End of trial
Study acceptability (both groups)	Study participation questionnaires (adolescent and parent) Qualitative interviews (adolescent and parent)	5	End of trial

*Measures relating to parental outcome.

BRIEF-2, Behaviour Rating Inventory of Executive Function, Second Edition; CBQ, Conflict Behaviour Questionnaire; CHU-9D, Child Health Utility 9D; CSRI, Client Service Receipt Inventory; EQ-5D-5L*, EuroQol 5 Dimensions 5 Levels Questionnaire; GAD-7*, Generalised Anxiety Disorder 7-item; PHQ-9*, Patient Health Questionnaire 9; RCADS, Revised Child Anxiety and Depression Scale; SDQ, Strengths and Difficulties Questionnaire; TAU, treatment as usual.

